[figure not shown]

**3. Abbreviations**

| CAMHS | Child and Adolescent Mental Health Service |
| --- | --- |
| DAWBA | Development and Wellbeing Assessment |
| GAD-7 | Generalised Anxiety Disorder Questionnaire |
| GOSH | Great Ormond Street Hospital |
| GP | General Practitioner |
| NHS | National Health Service |
| PHQ-9 | Patient Health Questionnaire |
| R&D | NHS Trust R&D Department |
| SDQ | Strengths and Difficulties Questionnaire |
| Peds-QL | Pediatric Quality of Life Inventory |
| UCL | University College London |

# Study Synopsis

| Title |  | Psychological Wellbeing Drop-In Centre at Great Ormond Street Hospital: A Service Development Research Project. |
| --- | --- | --- |
| Sponsor name |  | Great Ormond Street Hospital for Children NHS Foundation Trust |
| Primary objective |  | Do young people and their parents/carers find a drop-in centre for emotional/behavioural health at Great Ormond Street Hospital useful? |
| Secondary objective (s) |  | To evaluate a drop-in centre in terms of (i) the number of people accessing such a service, (ii) satisfaction, (iii) usefulness and, where possible, (iv) impact on physical health and (v) value for money. |
| Study Design |  | Questionnaire study |
| Study Endpoints |  | The final follow-up (6 months) of the final participant. |
| Sample Size |  | 5000 |
| Summary of eligibility criteria |  | *Inclusion criteria:* Patient at participating sites or carer or family member of a patient at participating sites.  *Exclusion criteria:* Patient must have attended one of the participating sites within the last six months. |
| Procedures: Screening & enrolment |  | The signs for the drop-in centre will make it clear that this is a research project. Young people and families may make the first approach to the research team who will sit in the centre, or the clinical research team may approach potential participants in public areas of the hospital by handing out leaflets to advertise the research. In addition, where interest is expressed and consent given, members of a patient’s direct clinical care team may sign-post or refer young people and parents/carers to the centre. No patient identifiable information will be accessed by the research team in order to approach potential participants in the hospital. Potential participants will be given written and verbal information about the project and will have the opportunity to discuss the research and ask any questions. Written informed consent (and assent where applicable) will be taken by a member of the clinical research team where appropriate. Participants may also wish to give consent via email or over the telephone if they have made the first contact with the research team by these means (e.g. after reading an advertising leaflet or poster for the study). |
| Clinical Intervention |  | The drop-in centre is funded as a research project and is currently not part of existing clinical services. If the project is successful and the centre is well-received, acceptable and effective then it will be incorporated into routine clinical practice. Therefore, we are viewing the intervention provided by the centre as research.  The intervention will vary depending on individual needs but is likely to include assessment, signposting to charities and support agencies and provision of evidence based low-intensity psychological interventions for common problems e.g. anxiety, sleep problems and behavioural difficulties.  The drop-in centre will be staffed by a qualified Psychological Wellbeing Practitioner, trained volunteers, a clinical psychologist and members of GOSH clinical teams (e.g. paediatric liaison) as appropriate. All staff will receive regular supervision from an experienced clinical psychologist, and will have access to the duty psychiatrist. |
| Measures |  | Mental health screening measures:   - Strengths and Difficulties Questionnaire (SDQ) - Patient Health Questionnaire (PHQ-9) - Generalised Anxiety Disorder Questionnaire (GAD-7) - Pediatric Quality of Life Inventory (Peds-QL)   Drop-in Centre Satisfaction Questionnaire  ONCE OFF – activity feed-back form |
| Follow up Measures |  | Mental health screening measures:   - Strengths and Difficulties Questionnaire (SDQ) - Patient Health Questionnaire (PHQ-9) - Generalised Anxiety Disorder Questionnaire (GAD-7) - Pediatric Quality of Life Inventory (Peds-QL)   Drop-in Centre Follow-Up Questionnaire (6 months after initial contact with centre). |
| End of Study |  | End of study is the last follow-up of the final participant. |

1. **Background**

Young people with physical illnesses are at significantly greater risk of developing emotional and behavioural problems than the general population. Such problems not only impact significantly on young people and their families, but can also have negative consequences for the management and course of the physical illness. Psychological treatments are highly effective for young people and adults but they are difficult to access. Parents and carers have also said that they find it difficult to access appropriate support for themselves when their child is physically unwell. There has been a recent drive to integrate physical and mental health care to improve access to evidence based psychological treatments.

The overarching aim of this research is to establish the usefulness of a Psychological Wellbeing Drop-In Centre at Great Ormond Street Hospital (GOSH). We aim to deliver a friendly, accessible drop-in centre at the heart of public areas at GOSH where young people who are patients at the hospital and their carers can access advice about common emotional, behavioural and mental health problems. Families accessing the drop-in centre may receive a range of support from a team of trained mental health professionals including:

- Evidence based assessment of mental health difficulties
- Signposting to relevant services and third sector organisations
- Information and resources about common emotional and behavioural difficulties
- ‘Low intensity’ evidence based interventions for mild mental health problems e.g. anxieties, behavioural management and sleep problems.

The drop-in centre is not currently an existing service but if this project is successful and the centre is well-received, acceptable to patients and effective then it will be incorporated into routine clinical practice.

**6. Specific Aims of the Study**

The aim of this study is to offer children and young people, and their families, quick and effective advice on their wellbeing and mental health needs. We are trying to improve the mental health and psychological wellbeing of any child attending participating sites who needs this support and ensure that any mental health needs are detected, diagnosed and treated.

The principal research question is: Do young people and their parents/carers find the drop-in centre for emotional/behavioural health at participating sites useful?

The secondary objectives are to evaluate the drop-in centre in terms of (i) the number of people accessing such a service, (ii) satisfaction, (iii) usefulness and, where possible, (iv) impact on health and (v) value for money.

1. **Study Design**

This is a feasibility study that is designed to assess user satisfaction and usefulness. All participants will receive the intervention from the drop-in centre in addition to treatment as usual.

Young people and parents/carers who approach the drop-in centre, or people in public areas of the hospital that are approached by the clinical research team and given a leaflet about the research, will be invited to participate. In addition, where interest is expressed and consent given, members of the patient’s direct clinical care team may sign-post or refer young people and parents/carers to the centre.

We will collect baseline data about young people and parent’s mental and physical health (SDQ, PHQ-9, GAD-7 and PedsQL measures) prior to their use of the drop-in centre in order to characterise the sample and identify the most common presentations.

The drop-in centre will provide evidence based information and support about common mental health difficulties. This will include assessment of needs, signposting to charities and support agencies, referral to other services and provision of low intensity psychological intervention. Low intensity means the most effective, but least intrusive, time consuming and expensive intervention. As the centre is funded as research, we are viewing these clinical interventions delivered by the drop-in centre as research.

Following their use of the centre, participants will be asked to complete brief questionnaire/s to provide feedback on the service they received (Drop-In Centre Satisfaction Questionnaire and/or the ONCE OFF – activity feed-back form). They will also be asked for permission to contact them in six months to complete additional mental health measures (SDQ, PHQ-9, GAD-7 and PedsQL) and to further establish the usefulness of the Drop-In Centre in terms of further action (e.g., did they follow up on any of the information given), impact on physical health and use of physical or mental health services (Drop-In Centre Follow Up Questionnaire).

The number of people using the pod over the period of the project will be assessed.

1. **Participants**

All young people and parents/carers that either approach the Psychological Wellbeing Drop-In Centre or are approached by the clinical research team at GOSH will be potential participants.

## Sample Size

5000. In 2014/2015, GOSH had more than 240,000 patient visits a year (outpatient appointments and inpatient admissions) and each of those patients will be accompanied by a carer bringing the total number of people eligible to access the pod to approximately half a million. If only 1% of these access the pod, this would translate to approximately 5000 per annum or 100 people per week.

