**10.2. Study Duration**

The study will last for 2 year, 11 months and 30 days in total (02/01/2017-31/12/2019). The study duration for each participant will be a maximum of 6 months (from initial drop-in to following up on impact of drop-in centre 6 months later).

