**10.3. Definition of End of Study**

The end of study is the date of the last contact (i.e. 6 month follow-up) for the last participant.

1. **Statistical Considerations**

The number of people using the service and their feedback on it are the primary outcome measures for the feasibility study. This will include mean satisfaction ratings and written descriptions of the usefulness of the drop-in centre.

We will also look at the mean scores on the SDQ, PedsQL, PHQ-9 and GAD-7 in order to characterise the sample.

We will review medical records (with participants permission) over a six month period to categorise (a) the nature of the contact with the drop-in centre; (b) number of referrals to other services; and (c) number of hospital appointments over the six month follow-up period.

We will use t-tests and repeated measures analysis of variance to compare changes in mental and physical health over the six month follow-up period.

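### The sample size of 5000 is a one-year figure built on hospital visits counted as people, yet it is stated for a study of about three years

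*Protocol*

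**What the plan says.** The synopsis gives the sample size as a bare 5000. Section 8, Sample Size, shows where it comes from. The base is a count of visits in 2014/2015: "GOSH had more than 240,000 patient visits a year (outpatient appointments and inpatient admissions". One carer is added for each, "bringing the total number of people eligible to access the pod to approximately half a million". Then: "If only 1% of these access the pod, this would translate to approximately 5000 per annum or 100 people per week".

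Section 10.2 fixes the calendar: "The study will last for 2 year, 11 months and 30 days in total (02/01/2017-31/12/2019". It adds: "The study duration for each participant will be a maximum of 6 months". Section 10.3 ends the study at the last participant's six-month contact.

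Section 11 gives the figure a role beyond planning: "The number of people using the service and their feedback on it are the primary outcome measures for the feasibility study". The synopsis and Section 6, by contrast, make usefulness the principal question and list the number of people accessing the service as a secondary objective. Section 7 says that users will be counted over the period of the project.

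**The concern.** Two slips sit in one number.

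- **Time base.** The derivation ends in a yearly figure, and that figure is then used as the sample size of a study about three years long.
- **Unit.** The base counts appointments and admissions, but the text treats each one as a separate patient with a separate carer. A child who attends several times a year enters the pool several times, and so does the carer. Participants are people: Section 15 gives each one a single study number at entry. The 1% therefore sets people against a pool made of visits.

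This derivation is the only planning benchmark for uptake in the protocol, and Section 11 makes the number of users part of the primary outcome. If 5000 people use the centre by the end, the protocol does not say whether that meets the expectation (one year's figure) or is about 40% of it (some two and a half years at the stated rate). The background says that a successful and well-received centre will enter routine practice, so the benchmark should be well defined.

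**Working it through.** **Inputs from the Protocol.** More than 240,000 visits a year, one carer each, a pool rounded to 500,000, uptake 1%, and 5000 per year or 100 per week (Section 8). Dates 02/01/2017 to 31/12/2019 and six months per participant (Section 10.2).

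**Assumptions.** (a) If all follow-up falls inside the study dates, entry closes about 30/06/2019. (b) Visits per patient per year, k, is not given; a range of 2 to 5 is used.

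**Step 1: reproduce the stated figure.** 500,000 × 0.01 = 5000 per year, which matches. The unrounded lower bound gives 2 × 240,000 × 0.01 = 4,800 per year. The 4% gap is covered by the text's own hedges, since it gives the visits as a minimum and the pool as approximate. Weekly: 5000 / 52 = 96 and 5000 / 50 = 100. The arithmetic is sound for one year on a pool of visits plus carers. All percentages below refer to that doubled pool; as a share of visits alone, 5000 / 240,000 = 2.1%.

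**Step 2: length of the study.** Full period, both end dates included: 1,094 days = 156.3 weeks = 2.995 years. To 30/06/2019: 910 days = 130 weeks = 2.491 years.

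**Step 3: correct the time base only.**

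| | Entry to 30/06/2019 (assumed) | Full period |
|---|---|---|
| Users at 5000 per year | 5000 × 2.491 = 12,457 | 5000 × 2.995 = 14,976 |
| Users at 100 per week | 100 × 130 = 13,000 | 100 × 156.3 = 15,629 |
| Weekly rate if 5000 is the total | 5000 / 130 = 38 | 5000 / 156.3 = 32 |
| Yearly uptake if 5000 is the total | 5000 / (500,000 × 2.491) = 0.40% | 5000 / (500,000 × 2.995) = 0.33% |

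With the 480,000 pool the yearly uptakes are 0.42% and 0.35%.

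**Step 4: correct the unit only.** People per year at 1% = 0.01 × 500,000 / k: 2,500 at k = 2, 1,667 at k = 3, 1,250 at k = 4 and 1,000 at k = 5. Equivalently, 5000 people in one year would need an uptake of k%, for example 2% at k = 2 and 5% at k = 5.

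**Step 5: correct both.** Over the full period, 14,976 / k gives about 7,500 (k = 2), 5,000 (k = 3), 3,750 (k = 4) and 3,000 (k = 5). The two corrections cancel near k = 3, or near k = 2.5 for the shorter entry window, because k then equals the number of years. Multiplying by years also assumes that each year's users are new people; returning users would lower these totals.

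**The case against.** The strongest defence is that this is a rough projection for a feasibility study. No power or precision calculation depends on it, the 1% is put as a conditional, and the stated arithmetic reproduces. Users and consented participants may also be different counts. Section 9 invites everyone who enters and expects no consent at first arrival, so about 12,500 users with 5000 consents (5000 / 12,457 = 40%) would fit the dates and the rate.

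Part of this stands. The documents do not exclude such a reading, so the figures are not proved irreconcilable. But Section 8 takes 5000 directly from the number accessing the centre and applies no consent rate, so the reading has to be supplied from outside the text. The informality of a projection does not excuse a wrong time unit or a change from visits to people.

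A reader might go further and infer that 5000 caps enrolment and so truncates the user count. The documents do not support that. Nowhere is 5000 called a maximum, the only discontinuation criterion (Section 12) concerns people declining consent, and Section 7 counts users over the whole project. Nor would a final count of 5000 be uninterpretable. Follow-up is timed from first contact, so contact dates must be known, and 5000 users in one year can be told apart from 5000 over two and a half.

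**Conclusion.** The point holds as an error of time base and unit in the stated sample size. At the protocol's own rate the expected number of users is about 12,500 to 13,000 (entry closing six months before the end, assumed) or about 15,000 to 15,600 (full period), that is, 2.5 to 3.1 times the stated 5000. Counting people instead of visits divides the projection by k, which the protocol does not give. The two errors act in opposite directions, so it cannot be said that 5000 is too high or too low, or that a corrected figure would look less favourable. If 5000 happens to be about right, that is by coincidence, near three visits per patient per year. The base also covers GOSH alone, while the eligibility criteria speak of participating sites, which adds to the uncertainty.

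It would be too strong to say that the error damages the study's single primary outcome. Section 11 names the user count together with feedback, and the synopsis and Section 6 place it among the secondary objectives. What is affected is the planning benchmark for uptake, not the count itself.

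**What to change.** In Section 8 and the synopsis:

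- Base the pool on unique patients plus carers, for the sites actually taking part and over the actual entry period, with the last entry date stated. The protocol does not say whether unique-patient counts are available. If they are not, give an assumed number of visits per patient and show the range.
- State whether 5000 is annual or total.
- State whether it counts users of the centre or consented research participants and, if the latter, the consent rate assumed.
- State that it is an expected number and does not limit the count of users over the project.

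The cost is one rewritten paragraph, a matching synopsis entry and a changed planning figure that may go up or down. The design and the planned data collection stay as they are.

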## Inclusion Criteria

Current patient at participating site, or carer of a patient at participating site.

## Exclusion Criteria

Patient must have attended their participating site within the last six months. Children/families who do not speak/understand English sufficiently well to access the resources and questionnaire measures will be excluded from this study. This is primarily due to limited funding capacities for interpreters, however, should sufficient additional funding by obtained, then we would seek to recruit these families and to hire interpreters to allow equitable access to the intervention.

# Recruitment and Informed Consent

The signs for the drop-in centre will make it clear that this is a research project. Young people and their families may make the first contact with the research team, or the clinical research team may approach potential participants and give them a leaflet to inform them of the study. No patient identifiable data will be accessed by the research team in order to approach potential participants. It is possible that members of their direct clinical care team may signpost or refer them to the drop-in centre if they think that the family may benefit from taking part in the research. Any young person or parent/carer that enters the drop-in centre will be invited to participate by a member of the clinical research team. They will inform the family about the study and give written information to interested participants. As there are no strict inclusion/exclusion criteria no medical records will be screened by the research team at this stage.

The appropriate information sheet will be given to all potential participants, informing them about the study, and what participation will involve. An information sheet will be given both to the young person and their parent/caregiver if they are under 16. Separate REC approved information sheets will be provided for parents/carers and young people of different age ranges. They will be provided with contact details of the research team should they wish to discuss this further or ask any questions. They can choose to consider participation and return another time and there will be no expectation that potential participants will consent on their first arrival at the centre.

Participants will be given the opportunity to ask any questions and only once all of their queries have been answered will consent be taken by the principal investigator or suitably qualified, delegated member of the clinical care team.

We will obtain informed consent from all participants prior to taking part in the study. Written informed consent will be received from most participants. However, some participants may wish to consent via email or telephone if they have made first contact with the research team by these means (e.g. after picking up an advertising leaflet). Participants will then be invited to attend the drop-in clinic where they will follow the usual procedure including assessment, completion of questionnaire measures and provision of low-intensity interventions. Some of these procedures may be completed remotely, as per usual procedures (e.g. one possible intervention may be guided self-help provided over the telephone).

If the participant is not able to consent for themselves, they will provide informed written assent and a parent/guardian will provide written informed consent on their behalf.

We will make it clear to all potential participants that their usual care will not be affected by their decision to participate. A list of services and information about what to do in an emergency (e.g. access to out-of-hours GP and A&E) will be available to all potential participants.

**10. Procedure**

Mental Health Measures

Following written consent, participants will be asked to complete up to three brief screening measures of mental health as follows:

**SDQ:** This is a brief screening questionnaire for common mental health problems in young people. It will be completed by parents only if the child is under 11 years, or by both the parent/carer and child if the child is aged 11 years or over. It will be completed in the drop-in centre

**PedsQL**: This is a brief assessment measure of young people’s quality of life. It will be completed by the parent/carer only if the child is under 8 years, or by both the parent/carer and child if the child is aged 8 years or over.

**PHQ-9:** This is a brief screening measure for depression in adults. It will be completed by parents/carers to assess parental mental health for children under 12. Children 12 years or over will complete this measure to assess child mental health.

**GAD-7:** This is a brief screening measure for anxiety in adults. It will be completed by parents/carers to assess parental mental health for children under 12. Children 12 years or over will complete this measure to assess child mental health..

The SDQ, PedsQL, PHQ-9 and GAD-7 are all routinely used in clinical practice.

Participants will complete these measures either in the clinic, over the telephone, via email or online in Redcap according to patient preference.

Planned Interventions

Families will have the opportunity to outline their concerns to a trained mental health professional. Depending on the nature of the difficulty, possible outcomes might be:

- Standardised assessment using web-based, evidence-based brief measures including opportunity to access a widely used standardised online detailed assessment of child mental health (Development and Wellbeing Assessment; DAWBA) and obtain an assessment report;
- Provision of information or self-help material/website suggestions;
- Signposting e.g. where to find appropriate support agencies, charities etc.;
- Referral to appropriate services either within Paediatric Psychology or Psychological Medicine at participating sites, Psychiatry at participating sties or in the local vicinity of the family; and/or
- Brief focussed evidence-based advice for common mental health problems e.g. behaviour management, childhood fears, sleep problems.

Care Pathways

The drop-in centre will be staffed by (1) a member of the clinical research team qualified to deliver low intensity mental health interventions (a qualified ‘psychological wellbeing practitioner’); (2) a member of participating site or volunteer team who will have undergone prior training; and (3) depending on need and demand, members of the psychology, psychiatry, mental health and psychological teams at participating site who will provide sessional input to the centre.

All members of staff will have regular supervision by a qualified clinical psychologist. The duty psychiatrist for the hospital will be available at all times. The service would be closely linked to psychiatric liaison, paediatric psychology and the CAMHS department.

The drop-in centre will offer a ‘first step’ on the stepped care pathway. Some children and/or carers may be identified as having a significant mental health disorder warranting urgent/immediate treatment. Children/carers identified as having psychiatric symptoms will be referred to services as appropriate. Thus, children/carers who screen for a severe mental health disorder or whose screening questionnaire is otherwise suggestive of risk will be referred to other services as appropriate, consistent with best practice guidance. The research team comprises a number of trained clinicians, who will be well placed to liaise with, and refer to, other services. This may include (although is not restricted to) local CAMHS, the participating site. Psychological Medicine Team or Paediatric Psychology. This procedure will also be followed should it become apparent that there is risk (including harm to self and others) during the course of the research. Liaison will continue until the risk is adequately managed.

Satisfaction and Follow-Up

Following use of the Drop-In Centre, participants will be asked to complete the Drop-In Centre Satisfaction Questionnaire and where a single-session intervention was provided: the ONCE OFF – activity feed-back form. These will be completed by the parent/carer only if the child is under 11 years, or by parent/carer and child if child is aged 11 years or over (8 years or over for the ONCE OFF – activity feed-back form). Participants may also be interviewed about their experience of trying to access support, their pathway to the centre and their experience of the support provided.

We will ask permission from all participants to contact them again in six months time to ask them for additional feedback on the centre. The Drop-In Centre Follow-Up Questionnaire will be sent by post or email according to participant preference six months after their first contact with the Centre. This will be completed by the parent/carer only if the child is under 11 years, or by parent/carer and child if child is over 11 years. It will be completed in participants own home and returned by post or email according to participant preference.

Medical records will be reviewed to characterise the nature of the intervention received from the drop-in centre, and number of appointments or referrals to other services during the six month follow-up period. Written consent will be sought prior to anyone outside of the direct clinical care team gaining access to participants' personal data.

